## Abstract

**Introduction:**

Epithelioid hemangioendothelioma (EHE) is an ultra-rare sarcoma, marked by distinctive molecular and pathological features and with a variable clinical behavior. Its natural history is still partially understood, reliable prognostic and predictive factors are lacking and many questions are still open on the optimal management. In the context of EURACAN, a prospective registry specifically dedicated to EHE was developed and launched with the aim of providing, through high-quality prospective data collection, a better understanding of this disease.

**Study design:**

Registry-based cohort study including only new cases of patients with a pathological and molecularly confirmed diagnosis of EHE

**Objectives:**

To improve the understanding of EHE natural history, validate and identify new prognostic and predictive factors, clarify the activity and efficacy of currently available treatment options, describe treatment pattern.

**Methods:**

**Results:**

The registry has been joined by 21 sarcoma reference centers across EU and UK, covering 10 countries. Patients’ recruitment started in December 2023. The estimated completion date is December 2033 upon agreement on the achievement of all the registry objectives. The already established collaboration and participation of EHE patient’s associations involved in the project will help in promoting the registry and fostering accrual.

## Introduction

Given its incidence of 0.038/100 000/year, EHE is an ultra-rare sarcoma, with distinctive, well-defined pathological, molecular and clinical features [1,2]. It belongs to the group of vascular sarcomas and is characterized by *WWTR1-CAMTA1* (90%) or *YAP1-*TFE3 (10%) gene fusions, which represents today a hallmark for diagnosis. EHE potentially arises everywhere in the body and shows a high tendency toward metastatic spread, especially in the lung, liver and bone [3,4]. The onset is characterized by different presentations, including a unifocal lesion (usually in the soft tissues), locoregional metastases (multiple lesions in a single organ or in a single anatomic compartment) and systemic metastases (multi-organ involvement) [4]. Also, the biological behavior of the disease is unique in sarcomas and variable, with spontaneous regressions reported, patients with untreated stable disease overtime, slowly progressive variants and highly aggressive and rapidly fatal cases. Today, the relative incidence of the different presentations is undefined, the natural history of the different subtypes is poorly understood, and reliable clinical or biological prognostic factors are lacking. Retrospective data suggest that patients with EHE presenting or developing during their course serosal involvement and / or effusion, systemic associated symptoms and anemia have a worse prognosis, but a prospective validation of this observation is lacking [5–7]. In terms of management, surgery is the treatment of choice for localized disease, with an excellent outcome (expected cure rate of 70–80%) and no proven role for local or systemic adjuvant therapies. For patients with advanced, asymptomatic disease, active surveillance is often the upfront choice in order to minimize the risk of overtreatment [4]. Systemic therapies are usually considered for patients with progressive or symptomatic disease, although a standard medical approach is currently not established. Unfortunately, conventional chemotherapy, including anthracycline-based regimens widely regarded as the mainstay in the treatment of advanced soft tissue sarcomas, showed marginal activity in EHE [8]. The use of potentially active compounds, such as *m-TOR* inhibitors which proved the highest activity in EHE and could therefore represent the preferred option, is limited by regulatory constraints as they are not currently labeled in Europe for this indication [4,6,9]. Given the degree of uncertainty on EHE management, a global consensus meeting was organized in December 2020 under the umbrella of the European Society for Medical Oncology (ESMO) involving > 80 multidisciplinary, worldwide experts together with a patient representative, with the aim of defining, by consensus, evidence-based best practices for the optimal approach to primary and metastatic EHE [4].

Since the number of patients is inherently low at the hospital level, the only way to increase knowledge about EHE and improve the diagnosis, treatment, and prognosis of this complex and heterogeneous disease is to harmonize and combine real-world data from sarcoma expert centers by leveraging a wide, international, joined effort. In this context, a unique opportunity is provided by the European Reference Networks (ERNs), virtual network established by the EU commission aiming to tackle rare conditions, including cancers. Among the three ERNs dedicated to cancer, EURACAN (https://euracan.eu) is the one focusing on the 10 families of rare adult solid cancers (RACs), including soft tissue sarcomas, bone sarcomas and gastrointestinal stromal tumour. Fostering academic research and promote epidemiological surveillance in rare cancers through setting up of shared registries is recognize as one of ERNs priorities. This is why within EURACAN the EU-supported project named “Starting an Adult Rare Tumour Registry (STARTER)” began on April 1st 2020 to develop the EURACAN registry dedicated to the RACs (https://euracan.eu/registries/starter/). The registry it is now running, and since May 2022 is open to data collection on rare head and neck cancers (ClinicalTrials.gov Identifier: NCT05483374). Within the sarcoma domain, taking into account the challenges described above, priority was given to ultra-rare sarcoma, and thanks to the strong connection, motivation and support provided by EHE Rare Cancer Charity UK, it was decided to start from EHE. We believe that in this context the collection of high-quality data by clinical registries will be crucial to improve the understanding of EHE natural history, validate and identify new prognostic factors, clarify the activity and efficacy of currently available treatment options and eventually provide and external control which might serve as a benchmark for the development of new drugs and support discussion with regulatory authorities.

EHE registry objectives:

To describe EHE population and diseases characteristics at diagnosisTo define EHE natural history, as a whole and in its variantsTo describe EHE response to different systemic therapies and radiation therapyTo assess effectiveness of different treatments (surgery, radiation therapy, systemic therapies, ILP, locoregional techniques and combination)Identify prognostic and predictive factors including:
○ Age at diagnosis, gender, hormonal status (for females), performance status○ Disease extent at presentation, disease size (for primary localized tumours) and disease site [4,7,10,11]○ Signs and symptoms at presentation and during follow up, including tumour-related pain, systemic symptoms (such as temperature, asthenia, anorexia, weight loss, night sweating) and limb edema [7]○ Anaemia and fibrinogen increase [12]○ Radiological features (including serosal involvement and / or effusion) [6,7]○ Pathological features (including necrosis, mitoses, nuclear pleomorphism) [10,13]○ Molecular features (including molecular translocations, *WWTR1-CAMTA1* vs *TFE3-WWTR1* vs others) [11,14,15]To describe treatment pattern and adherence to consensus paper recommendations on EHE clinical management (including diagnostic ascertainment, treatment, follow-up) [4]

To generate hypotheses on potential risk factors: demographics, sex, medical history (allergy, previous malignancies, immune-mediated diseases and previous immunosuppressive therapies, hormonal influence).

## Methods

### Setting and participants

#### Data collection

The EURACAN EHE registry is a prospective clinical registry that will collect data from all new patients receiving a pathological and molecularly confirmed diagnosis of EHE starting from the 1^st^ December 2023. To this aim, an EHE-focused clinical record form (CRF) was developed through the Research Electronic Data Capture (REDCap) and designed to capture the specific features of this disease.

For each patient, data collection will include:

1- A common baseline, including full details on demographic, comorbidities (special focus on immune-mediated and gynecological diseases), concomitant medications, physical examination, systemic symptoms at presentation, tumour-related pain assessment, blood tests, pathology and molecular features (on the diagnostic specimen), EHE extension at baseline (unifocal disease, loco-regional disease, systemic metastases)2 Depending on the disease extent, detail on staging modalities, primary site and size, extension of metastatic disease (organs involved, number of lesions), presence and characterization of serosal involvement and effusion, treatment (surgery, radiation therapy, medical therapies, isolated limb perfusion, other locoregional techniques)

Although the EHE registry per se does not foresee any collection of pathological samples and / or imaging, the availability for each enrolled patient of pathological samples, massive parallel sequencing data and imaging at the contributing institution will be captured by the registry, in order to facilitate patients’ identification for future dedicated studies which will imply the use of these data.

Given the peculiar biological EHE behavior, in absence of any event, a mandatory 6-monthly update will be required at all contributing centers. In the mandatory 6-monthly update, information from the last visit will be recorded regarding: physical examination, time interval of development of systemic symptoms, assessment of tumor-related pain, blood tests, update on ongoing treatment / active surveillance (including modalities and timing of radiological monitoring and radiological response).

All events will be recorded at the time of the occurrence (for unifocal disease, local recurrence and metastatic progression; for locoregional and metastatic disease, systemic progression). For every event, information will be recorded on physical examination, time interval of development of systemic symptoms, assessment of tumor-related pain assessment, blood tests (hemoglobin and fibrinogen), radiological modalities detecting progression, extent of progression (by RECIST 1.1 and not) [16], serosal involvement and / or effusion, update on ongoing treatment / active surveillance.

Patient status (alive with no evidence of disease, alive with disease, dead) and last follow up will be updated at any data entry.

The registry and therefore the electronic CRF have been shaped starting from what have been agreed and reported in the EHE consensus paper from the sarcoma community of experts, published in 2021 [4]. A registry kick-off meeting was held in Milan the 15^th^ September 2023, involving the EHE prospective clinical registry coordination team, all the contributing centers and patients’ associations (EHE Rare Cancer Charity UK, EHE Italia and EHE US) to present the registry and share common clinical practice guidelines, derived from the consensus paper, to be followed for the patients with EHE included in the registry.

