### Outcomes are listed per registry objectives

EHE population and diseases characteristics at diagnosis (M/F ratio, average age, proportion of Charlson Comorbidity index, ECOG performance status, distribution of primary site and disease extension) [4]EHE natural history (cumulative incidence of local recurrence and distant metastases per different EHE extension; description of progression patterns: site of metastatic spreading, number and site of new lesions, evolution of known lesions, presence and features of serosal involvement, time to local progression or distant metastases; overall and progression free survival) [4,7]Treatment Effectiveness (overall response rate, by RECIST1.1 and according to clinical judgment, competitive cumulative incidence of local recurrence and distant metastases, disease-free survival, overall survival)Identify Prognostic and predictive factors: overall and progression free survival and treatment responseDescription of treatment pattern and quality of care: percentage of patients treated according to Consensus paper recommendations.

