#### Data analyses plan

The data analyses will include descriptive statistics and analytical analyses. Descriptive statistics will be used to reconstruct the natural history of EHE (e.g. cumulative incidence of local recurrence and distant metastases, proportion of site of metastatic spreading, number and proportion of site of new lesions, evolution of known lesions, presence and features of serosal involvement, time to local progression or distant metastases etc.) and to report indicators about quality of care (e.g. description of staging procedures, description of treatment pattern, etc.).

Multivariable Cox’s proportional hazards model and Hazard ratios (HR) for all-cause or cause-specific mortality will be used to determine independent predictors of overall survival, recurrence and progression. Variables to include in the multivariable regression model will be selected based on the results of univariable analysis and using Information Criteria, such as Akaike Information Criterion. According to the specific research question the role of potential confounders and effect modifiers will be evaluated. Sensitivity analyses will be performed to estimate the potential impact of confounders. Statistical interactions between predictors and the variable will be tested to detect potential effect modifiers and stratified analyses will be performed in case of presence of any effect modifiers.

To assess treatment effectiveness, propensity score adjustment will be applied to multivariable models to remove bias due to real world nature of the registry.

High proportion of missing data threaten the validity of the inferences/prognostic models. Thus, a maximum of 10% of missing data will be allowed and missing data will be imputed using strategy such as unconditional/conditional mean or expectation maximum. To minimize missing information, in addition to the prospective nature of the registry, summary lists of information to be collected during clinical visits and including all the pathological details required for diagnosis were shared with all centers.

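### The listed events for locoregional disease omit in-organ progression and local recurrence, although local-event incidence by extension, time to local progression and PFS are planned outcomes

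*Protocol article*

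**What the plan says.** Under Methods, Data collection, the protocol article states that events are entered when they occur and lists them by baseline extent: "for unifocal disease, local recurrence and metastatic progression; for locoregional and metastatic disease, systemic progression". Each event record then includes "radiological modalities detecting progression, extent of progression (by RECIST 1.1 and not", among other items. Where nothing has happened, "in absence of any event, a mandatory 6-monthly update will be required at all contributing centers". That update draws on the last visit and includes how and when imaging was done and what response it showed.

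The Introduction describes the presentations other than a unifocal lesion as "locoregional metastases (multiple lesions in a single organ or in a single anatomic compartment) and systemic metastases (multi-organ involvement".

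The outcomes section plans "cumulative incidence of local recurrence and distant metastases per different EHE extension". Under natural history it also lists time to local progression and PFS, none of them restricted to unifocal disease.

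Two further statements bear on the point. In Data collection: "Patient status (alive with no evidence of disease, alive with disease, dead) and last follow up will be updated at any data entry". In the Data analyses plan, in a sentence that opens by naming a multivariable Cox model: "Hazard ratios (HR) for all-cause or cause-specific mortality will be used to determine independent predictors of overall survival, recurrence and progression".

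**The concern.** The event list and the outcome list do not match. Unifocal patients have both a local and a distant event type. Locoregional patients have one event type, and its name points to spread beyond the organ or compartment. Growth of known lesions in that organ, new lesions within it, or recurrence there after treatment is the local part of the natural history the registry sets out to describe, yet none of these is a listed event for this group.

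At stake is the description of the disease by extent. If progression is entered at occurrence in one group and reconstructed from periodic updates in another, part of any difference in PFS between them comes from the recording rule. The article also hopes the data may serve as an external control for new drugs and support regulatory discussion. A PFS curve whose event definition changes with baseline extent would be hard to use for that.

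**Working it through.** The article gives no figure for this point, so the check sets each planned outcome against the items listed, by baseline extent.

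**Step 1. Listed events.**
- Unifocal: local recurrence; metastatic progression.
- Locoregional: systemic progression.
- Metastatic: systemic progression.
- All extents: death, through the patient-status item.

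**Step 2. Meaning of the term.** The article does not define systemic progression. Its nearest usage is in the Introduction, where systemic marks multi-organ involvement, in contrast to lesions within one organ or compartment. On that usage, a locoregional patient has the listed event only when disease appears outside the original organ or compartment.

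**Step 3. Outcomes against events.**

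| Planned outcome | Unifocal | Locoregional | Metastatic |
|---|---|---|---|
| Local recurrence or local progression | Listed event | Not a listed event | Not listed separately; may be read from the extent item if any progression counts |
| Distant metastasis or spread | Listed event | Listed event | Covered if the term means any progression of systemic disease |
| PFS | Covered: recurrence, metastasis, death | In-organ progression missing | Covered on the same reading |
| Overall survival | Covered | Covered | Covered |

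The clear gap is the locoregional column.

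**Step 4. Other routes into the data.** The extent-of-progression item belongs to the event record, so it exists only once an event has been triggered. The 6-monthly update is filed when no event has occurred, and it carries imaging timing and response. An in-organ progression can therefore be found there and given an approximate date, but through a visit-based summary and not a named progression event. Unifocal progression is entered at occurrence; locoregional in-organ progression would have to be rebuilt from updates six months apart.

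**Step 5. Direction and size.** A missed or late event moves the PFS curve upward. The documents give no share of first events that are in-organ, so the size is unknown. For illustration only, assume:
- a share *f* of all first PFS events, deaths included, is never captured;
- hazards are proportional across event types;
- the hazard of the recorded events does not change after an uncaptured progression.

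Then recorded PFS = (true PFS)^(1−*f*).

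| True PFS | *f* = 0.25 | *f* = 0.50 | *f* = 0.75 |
|---|---|---|---|
| 50% | 0.5^0.75 = 0.595 (59%) | 0.5^0.50 = 0.707 (71%) | 0.5^0.25 = 0.841 (84%) |
| 70% | 0.7^0.75 = 0.765 (77%) | 0.7^0.50 = 0.837 (84%) | 0.7^0.25 = 0.915 (91%) |

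The values of *f* are arbitrary. For a given *f*, the table overstates the effect if the 6-monthly update recovers some events, or if recorded events follow faster after an uncaptured progression. It shows direction and is not an estimate.

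**The case against.** The strongest reply is that the event list is a short parenthesis summarising an EHE-specific eCRF that is not shown. The same sentence opens by promising that all events are recorded, and systemic progression is never defined, so carrying a definition of presentation over to it is an inference. The outcomes section also lists the number and site of new lesions and the evolution of known lesions, so in-organ change is evidently intended to be captured.

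Part of this stands. The eCRF may be finer than the article, so it would be too strong to say that these outcomes cannot be obtained. The article's own rule still separates event types by extent and gives locoregional disease only one. The intention to describe in-organ change makes that omission more of a conflict, not less.

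A reader might infer more than the documents support:

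- **PFS is lost throughout.** It is not. Unifocal PFS is covered. In patients whose disease is already multi-organ, progression is naturally systemic progression.
- **Local progression would be undated.** The 6-monthly update records when imaging was done, so the date is visit-based.
- **Cause-specific mortality cannot be computed.** A status item with a single category for death does not show that no cause-of-death field exists elsewhere. The analysis section offers cause-specific mortality as an alternative to all-cause mortality, and overall survival is unaffected.
- **Mortality hazard ratios are meant to identify predictors of recurrence.** The sentence can be read that way, but it also names Cox models, and the outcomes section plans competing-risk cumulative incidence, which needs only death from any cause. This is a matter of wording.

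**Conclusion.** The point holds for locoregional disease. On the article's own usage of systemic, progression confined to the same organ or compartment, or local recurrence after treatment, is not a listed event in that group, while the outcomes section plans local-event incidence by extension, time to local progression and PFS. The items listed do not support local-event incidence there. PFS tends to be late or overstated and is not comparable with unifocal disease.

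This rests on two assumptions: that systemic progression carries the meaning the Introduction gives to systemic, and that the eCRF follows the event list as the article states it. If the term was meant to cover any progression in a non-unifocal patient, events would be captured, but the article would still need to say so and to separate local from distant events. The size cannot be derived from the documents. Cause of death and the wording of the Cox sentence are secondary clarifications.

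**What to change.** 1. In Data collection, replace the extent-specific event list with one list of dated event types for every extent: local recurrence or in-organ progression, new distant lesion, progression of known lesions, and death. If the term systemic progression is kept, define it.
2. In the outcomes section, define PFS as time to the first of these events in all extents, and state which event types count as local and which as distant for the cumulative incidence outcomes.
3. Back-fill patients already entered, using the imaging timing and response in their 6-monthly updates and the centre's own records.
4. State whether cause of death is collected, since the analysis section names cause-specific mortality and the listed status item has a single category for death.
5. Reword the Cox sentence so that recurrence and progression are modelled as their own events with death competing, in line with the competing-risk incidence already planned, and so that mortality hazard ratios are used only for survival.

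The cost is an eCRF edit, a note to the centres, back-fill work and a few sentences in the plan. Because the registry is federated and data are held locally, the back-fill falls on each of the 21 contributing centres. Recruitment opened in December 2023 and completion is estimated for December 2033, so the back-fill is smaller the sooner the change is made.
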